### 1.1.6 Existing data sources, records and assessment processes

Routine cohort data are recorded in a paper-based patient file and entered daily into a purpose-designed MS Excel database by a trained data entry operator. The demographic data collected include: age, gender, mobile phone number, highest level of education; country of origin; refugee status and governorate of origin if Syrian; and insurance status if Jordanian. Data on Syrian refugees’ date of arrival in Jordan, UNHCR registration and Ministry of Interior card status are also collected if appropriate. Socio-demographic data are recorded on household size and crowdedness, type of dwelling and household makeup including gender and highest level of education attained by household head. Factors affecting treatment access and adherence are also documented i.e. impaired mobility and whether living with a treatment supporter.

Clinical data collected at the patient’s first visit include medical history, family history of relevant NCDs, lifestyle factors (smoking, alcohol consumption and exercise levels) and baseline vital signs (BMI, waist circumference, blood pressure, heart rate, blood sugar level and cardiovascular risk score assessment). New diagnoses; numbers, types, doses and reason to adapt medications; recommended specialist referral; and referral for laboratory tests are recorded at the first and each subsequent clinical visit.

At review visits, nurses record repeat vital signs and laboratory results; health educators record current exercise levels, smoking status and current stage of change on the Prochaska and DiClemente stages of change model for behaviour change. Symptom and functionality scores are recorded before and after a course of individual counselling, using Generalized Anxiety Disorder 7-item Scale (GAD7), Patient Health Questionnaire for Depression (PHQ 9) and a locally devised four-item screening tool for PTSD. These tools will be revised in early 2017.

Operational data recorded include numbers of new and follow-up medical consultations per month, type of consultation (nurse, doctor, home visit team), number of referrals made, number of health education sessions attended and programme exits (death, defaulter, voluntary defaulter). The number of MHPSS discussion groups, psycho-education sessions and individual counselling sessions undertaken per month are also recorded.

In addition, MSF-OCA has recently completed primary analysis of a cross sectional population based survey of Syrian refugees living in Irbid Governorate, undertaken for separate purposes. Data from this survey will provide initial information on the reach of MSF’s NCD activities and existing coverage of the target population.

Costing data are recorded in standard MSF pharmacy consumption tools, logistics supply tools, human resources and budgeting tools.

# 2. Study rationale, aim and objectives

There is a lack of data on models of NCD care and limited evidence on implementation, effectiveness and feasibility of NCD care in the humanitarian contexts where MSF works. The identification of NCD care as the greatest unmet health need amongst urban-based Syrian refugees living in Irbid, and rising NCD patient load in other settings, prompted MSF-OCA to develop a primary care based model of NCD care. This model is focussed on limiting treatment interruption and complications of established disease, and has evolved over time in response to clinical and programmatic needs. Lessons learned from Irbid may be adapted for MSF’s programmes in other contexts where NCDs are responsible for significant morbidity and mortality. The findings may also be used in MSF’s external advocacy work related to the scale-up of primary-level NCD care provision and cost of NCD medications in Jordan.

The overall aim of the study is to evaluate a primary care based model of NCD care delivered by MSF in Irbid, Jordan in order to refine the model and to generate evidence on its feasibility, acceptability and effectiveness with a view to translating a similar model to comparable humanitarian settings. This care model (outlined in section 1.1) will be evaluated through review of clinical indicators using routine cohort data; routine cost data; and qualitative data collected from patients, care providers and from key stakeholders.

The specific objectives are to examine the:

*Reach* (coverage) of the NCD service and its components to the intended target population.

*Effectiveness* of the NCD service. RE-AIM defines effectiveness as: the impact of an intervention on important outcomes, including potential negative effects, quality of life, and economic outcomes. Since this intervention has evolved over time, we cannot assess the effectiveness or cost-effectiveness of a specific intervention or strategy using a pre-post design and we do not have a comparator group. Thus, we defined “effectiveness” for this evaluation as quality of care. This will be examined by identifying trends in clinical outcomes and quality of care indicators; exploring perceived benefits, unintended consequences, behavioural outcomes and evaluating economic outcomes (See Table 2 below).

*Adoption / acceptance* of the NCD service and its components (including medication adherence) by the organisation, setting, staff and patients, and consequent changes to behaviour and practice.

*Implementation* of the NCD service and its components including fidelity in terms of consistency of applying the defined guidelines and processes; guideline usability, adaptation of structures, processes and tools; and costs.

*Maintenance* of the NCD service and its components in patients, programme and organisation over time.

# 3. Methods

## 3.1 Description of the study sites

The study setting will be Irbid city in northern Jordan. Irbid governorate, with a population of over 1.7 million, borders southern Syria. 27% of the 1.27 million Syrians living in Jordan are located in Irbid governorate ^18^; of these, 135,280 individual Syrians are registered with the UNHCR as persons of concern ^4^.

The majority of registered Syrian refugees in Jordan live outside official refugee camp settings within the local community ^4^. Until policy changed in November 2014, non-camp-dwelling UNHCR-registered refugees were entitled to free primary healthcare, which was funded by UNHCR and delivered through the Jordanian public health system ^19–21^ . The Jordanian system consists of a mix of public and private healthcare. Public care is free to three categories of insured citizens: civil servants, military and those categorised as “destitute” ^22^. While camp-dwelling refugees are still entitled to free primary healthcare, out-of-camp registered refugees now pay a subsidised fee, approximately 35-60% of the cost, similar to that paid by uninsured Jordanians ^21,23^.

MSF and other non-governmental organisations support the Jordanian government and the UNHCR in providing health care for non-camp-dwelling refugees. However, evidence from repeated surveys suggests that, as demand exceeds current capacity, both access and costs have proven barriers to refugees accessing essential health care and medications ^20,21,24^. Currently, MSF is the only actor providing free, specialised NCD care in Irbid governorate.

The previously completed MSF household survey was conducted in Irbid governorate in northern Jordan. Most of the area is uninhabited, mountainous terrain. The majority of Syrian refugees live in urban and peri-urban areas of Irbid city or Ramtha town, while the remaining 40% live in rural areas.

This evaluation, including use of routine service data, will take place in the two vertical, primary care based MSF-supported clinics providing NCD care in Irbid city centre. The first clinic was opened in December 2014 within an MoH primary care facility in Ibn-Sena. The clinic is located on the first floor, accessed by stairs only. The second clinic opened in April 2015, alongside a private organization, Arab Medical Relief (AMR), in their facility at Ibn-Rushd. This is located in the basement of a major civic building, also accessed by stairs only. Both clinics may be reached by public transport. Each contains a reception desk, central waiting area, triage room, individual consultation rooms, a larger room for group education sessions and a pharmacy. Ibn-Sena also has a treatment room where diabetic foot care is carried out.

**Table 2. List of main indicators and data method/source based on RE-AIM**

| Objective (Questions) | Domain | Indicator | Methods  (a single methodology may feature under several RE-AIM headings) |
| --- | --- | --- | --- |
| Reach  Does the programme reach its target population? | Coverage | Target population prevalence of diabetes & CVD  Number of people eligible for care for diabetes & CVD (inclusion/exclusion criteria)  Number of people receiving care for diabetes & CVD  Representativeness of those reached  Prevalence of NCD and identified, relevant MH comorbidity; eligibility for MHPSS services; numbers referred/receiving care; representativeness of those receiving MHPSS service | Existing cross-sectional survey previously conducted by MSF  Routine facility cohort data  2 focus groups with patients  Approximately 16 semi-structured patient interviews  Key informant interviews |
| Adoption/ initial acceptance  Is the MSF model of NCD care accessible and acceptable to patients, providers, organisation and community?  Is the MSF NCD guideline acceptable to staff? | Participation | Description of intervention location, cadres of staff and qualifications; inclusion/exclusion criteria of staff/settings delivering service  Sources and perceptions of information and support for participation in NCD service & components (e.g. HE, MHPSS)  Experience of receiving and providing NCD care including use of clinical guideline  How programme participation has influenced patient/staff well-being and staff ways of working. | Routine facility cohort data  2 Focus groups with patients  Semi-structured interviews with approximately 12 clinic staff and 16 patients |
|  | Accessibility/ acceptability | Duration and frequency of NCD service and components  Patient characteristics of those accessing individual programme components (e.g. HE, HLO, MHPSS, foot care)  Staff (e.g. ratio of staff per patient)  Structures and tools  Treatment continuity/rupture  Staff and patient perceptions of availability and accessibility / barriers to access of service components (clinical review, HE, HLO, MHPSS, HV, Foot care)  Staff perspectives on acceptability / usability of NCD guideline  Key stakeholder views on acceptability and accessibility of MSF NCD service and components (e.g. MSF, MoH, NGO staff,)  Self-reported medication adherence levels and medication beliefs | Routine facility cohort data  Key informant interviews  Participant observation  2 focus groups with patients  Semi-structured interviews with approximately 12 clinic staff and 16 patients  Self-report medication adherence questionnaire |
| Implementation  To what extent was the intervention delivered as intended?  What are the facilitators and barriers to implementing the programme from a patient, provider and programmatic perspective?  What are the essential components and adaptations necessary to delivering an NCD service in this setting?  What are the start-up and incremental costs of delivering such a service? | Fidelity of programme delivery  (Process Indicators;  indicators in bold also reflect quality of medical care) | Extent to which clinical guideline delivered as intended:  Number / % of eligible patients with HTN with annual FPG performed during the reporting period  Number/ % of eligible patients with diabetes that have had an annual foot check/ eye check performed during the reporting period  Number / % of DM patients that have micro-albuminuria or urinary protein testing during the reporting period  Number / % of DM patients on ACE inhibitor (ACEi) with Creatinine testing during the reporting period  Number/ % asthmatics and COPD with control review (spirometry or clinical) during the reporting period  Number / % of active cohort attending a health education session at last clinical visit within reporting period  Number of MHPSS group sessions taking place monthly during reporting period  Number/ % of referred patients attending MHPSS individual counselling sessions  Number/ % of times when clinical action taken based on clinical or laboratory findings according to guideline (see Annexe 2d for detail) | Clinical audit  Participant observation  Routine health facility cohort data |
|  | Adaptations | NCD care adaptations to the local setting (e.g. cultural adaptations; dietary and exercise, smoking advice)  Programme adaptations related to humanitarian setting and role e.g. response to patients’ psychosocial needs and NCD-relevant mental health co-morbidities | Key informant interviews  Participant observation  Semi-structured interviews with 12 MSF/clinic staff and 16 patients |
|  | Cost | Staff time  Start-up and recurrent implementation costs (indirect, intermediate and final cost centres)  Average unit costs and unit costs stratified by morbidity) | Key informant interviews  2 Focus groups with  Medicine/supply/ staff costs  Staff time estimates |
| “Effectiveness”/ Quality of Care  What are the trends in clinical outcomes and quality indicators of the programme?  What are the perceived benefits/unintended consequences from a patient and provider perspective? | Clinical Outcomes | No./% patients with hypertension that have a most recent BP <= 140/90 6 and 12 months post enrolment and trend from baseline  Number / % of patients with diabetes that have a most recent BP <= 140/90 6 and 12 months post enrolment and trend from baseline  Number / % of patients with diabetes with last HbA1c < 8.0 %/ 7.0 % 6 and 12 months post enrolment and trend from baseline  Number/% with a reduction of >= 0.5 mmol/L in cholesterol level from baseline 6 and 12 months from enrolment  Number/% of patients with asthma / COPD free from exacerbations/ admissions in the previous 6 months  Number / % of patients who report decreased/quitting smoking within reporting period  Number / % of patients who report increased levels of exercise from baseline during reporting period  Trend recommended referrals to another facility for acute complications/specialist care, as a proportion of active cohort | Routine facility cohort data  Costing data (for incremental costing analysis)  2 Focus group with patients  Semi-structured interviews with approximately 12 clinic staff and 16 patients |
|  | Quality Indicators | Proportion of recommended referrals to other services that are appropriate as per guideline  Number/ % of active patients with CVD prescribed a statin during reporting period  Number/ % of patients with CVD prescribed aspirin during reporting period  Number/ % of patients with CVD prescribed at least one anti-hypertensive during reporting period  Number/% of patients with COPD/asthma with inhaler technique check documented  Number/ % of times when appropriate clinical action taken based on clinical or laboratory findings according to guideline (see Annexe 2d for detail)  Trend in defaulters as a proportion of active cohort during reporting period  Description of cohort deaths (patient characteristics) | Clinical audit  Participant observation  Routine health facility cohort data |
|  | Perceived Effectiveness | Patient and providers perspectives on effectiveness of programme components (clinical review, medications, HE, HLO, MHPSS, HV) | Key informant interviews  2 Focus groups with patients  Semi-structured interviews with 12 MSF/clinic staff and 16 patients |
| Maintenance  What are the challenges and facilitators for patients to remain in the programme?  What are the costs involved in maintaining the programme?  What are the programmatic challenges and adaptations made to maintain the programme? | Individual Level | Number/% of patients active 6 months post enrolment in reporting period  Numbers of medications and daily pill count at last consultation during reported period  Self-reported medication adherence rates and medication beliefs  Qualitative measure of individual-level maintenance:  Key challenges in maintaining medical treatment (including medication concordance)  Key challenges in altering lifestyle (diet, exercise, smoking)  Key mental health/ psychosocial challenges  Types of support available and strengths and challenges of the support (health education, MHPSS, HLO, family and community support) | Routine facility cohort data  Clinical Audit  Key informant interviews  2 Focus groups with patients  Semi-structured interviews with 12 MSF/clinic staff and 16 patients  Medicine/supply/staff costs  Staff time estimates  Self-report medication adherence questionnaire |
|  | Organisational Level | Measures of cost of maintenance  Institutionalisation of the programme/modifications made for maintenance  Alignment with organizational mission |  |

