Health promoters provide individually tailored health education at each clinical contact. Topics covered include: education about diagnosis and disease, treatment and adherence support, patient concerns and expectations, and lifestyle changes. Motivational interviewing techniques are used to support patients to make lifestyle modifications related to diet, exercise levels and smoking. On enrolment, the doctor and health educator see patients for thirty minutes each; patients on return visits spend approximately fifteen minutes each with clinical staff (either a doctor or nurse) and a health educator.

Routine laboratory tests are carried out at a local laboratory, which has been quality assured by MSF. At the first visit a urine dipstick (for white cells, red cells and protein) is performed. A routine set of blood tests is carried out: haemoglobin (Hb), kidney function tests (sodium, potassium, creatinine), fasting blood glucose, liver function tests (LFTs), cholesterol profile (total cholesterol and triglycerides), glycosylated haemoglobin (HbA1c) and microalbuminuria for known diabetics, and thyroid function tests (free thyroxine and thyroid stimulating hormone) for patients with known thyroid disease. Fasting plasma glucose and HbA1c are repeated at 3-monthly intervals for diabetic patients; urine dipstick is repeated biannually; and cholesterol profile, kidney function tests and microalbuminuria are repeated annually. The other named tests are repeated as required according to clinical protocols.

Medications are those that are considered standard of care in Jordan; most are on the MSF Green List, the list of medications approved for use in MSF projects, with some additions relevant to the local context. Medications are dispensed from the MSF pharmacy, located onsite at each clinic immediately following a medical consultation. Prescriptions are renewed at maximum one-monthly intervals. Patient data are maintained in paper-based purpose-designed chronic care files, which are stored securely at each clinic.

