### 1.1.5 Programmatic Changes over Time

Specific additions were made to the programme over time in response to patient and programmatic needs. A home visit service, which commenced in August 2015, comprises a doctor, nurse and driver. It operates six mornings a week and serves frail or immobile patients living within a ten-kilometre radius of the clinics. 150 patients have been enrolled. They are seen on a monthly basis initially; stable patients may be reviewed by phone and visited less frequently.

A humanitarian liaison officer (HLO) was employed in August 2015 to assist vulnerable patients with social issues and direct them appropriately to services provided by other humanitarian actors. Patients are referred to the HLO by the medical team or the mental health service.

A mental health component was added in April 2016 to serve patients with NCDs and relevant, identified mental health co-morbidities, which may impact on their NCD care e.g. bereavement, anxiety or depression. Doctors and nurses can refer patients to the service. Two trained counsellors provide mental health and psychosocial support (MHPSS) through group psycho-education and discussion sessions and individual counselling. Group sessions take place in clinic waiting rooms and content is responsive to issues raised by patients. Individual sessions support patients’ medical treatment. Formal feedback structures between counsellors and medical staff have been introduced and will undergo review and refinement.

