### 3.4.1 Cohort study area and study population

The study location will be the two MSF-OCA supported clinics in Irbid city, northern Jordan. The first clinic was opened in December 2014 within an MoH primary care facility in Ibn-Sena and the second, opened in April 2015, works alongside a private organization, Arab Medical Relief (AMR), in their facility at Ibn-Rushd.

To date (November 2016), 4672 NCD-related patients (aged 1 to 94 years) have been registered in the two clinics, since patient registration was introduced in December 2014. Inclusion criteria are (1) Socio-demographic [Syrian refugee, refugee from another origin or vulnerable Jordanian (defined as patients who were identified as vulnerable according to the Ministry of Social Development National Aid Fund list) and (2) Medical [confirmed CVD (including angina pectoris, myocardial infarction, ischaemic stroke, peripheral vascular disease), CVD risk factors (HTN), COPD, Asthma and/or DM Type I or II]. Patients must fulfil both criteria. All NCD patients aged six years and older with at least two recorded visits (to enable evaluation of outcomes) will be included in the study cohort. This includes any new patients presenting with a new or existing diagnosis of a target NCD.

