### 3.4.2 Cohort study main outcome measures

The principal **clinical outcome measures** for patients in the cohort are:

DM: HbA1c < 7 or 8%; proportion of patients meeting individualised target at last visit within the reporting period and trend from baseline

Hypertension: BP < 140/90 mmHg: proportion of patients at target at last visit within the reporting period and trend from baseline

Cardiovascular disease: change in total cholesterol level from baseline

Asthma / COPD: Free from exacerbations / admissions in last six months

The principal **quality of care outcome measures** are the following:

Number/ % of active patients with CVD prescribed a statin during reporting period

Number/ % of patients with CVD prescribed aspirin during reporting period

Number/ % of patients with CVD prescribed at least one anti-hypertensive during reporting period

Number/% of patients with COPD/asthma with inhaler technique check documented

Number/ % of times when appropriate clinical action taken based on clinical or laboratory findings according to guideline (see Annexe 2e for detail)

Description of trends and patient characteristics in programme defaulters and deaths

Proportion of recommended referrals to other services that are appropriate as per guideline

Death is defined as confirmed death reported by family or community member. A defaulter is defined as a patient who has not attended any NCD clinic appointments within the last 90 days, is not known to have died or moved out of the area, and has not been successfully contacted by phone on two occasions by the clinic registrar. The definition was changed in October 2016 to reflect the newly extended appointment interval for stable patients to: two consecutive missed appointments; not known to have died, moved out of the area, or become immobile and ineligible for home care; and has not been successfully contacted by phone on two occasions by the clinic registrar.

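### Table 2 labels the most recent BP and last HbA1c as 6- and 12-month control with no limit on their age, and section 3.4.2 times the same outcomes differently

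*Protocol*

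**What the plan says.** Under clinical outcomes, Table 2 of the protocol lists "patients with hypertension that have a most recent BP <= 140/90 6 and 12 months post enrolment and trend from baseline" and "patients with diabetes with last HbA1c < 8.0 %/ 7.0 % 6 and 12 months post enrolment and trend from baseline". Neither row has a window, a maximum age for the value, or a condition that it be taken after enrolment.

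Section 3.4.2 names the principal outcomes and times them differently. For diabetes it is the "proportion of patients meeting individualised target at last visit within the reporting period and trend from baseline". For hypertension it is "BP < 140/90 mmHg: proportion of patients at target at last visit within the reporting period and trend from baseline".

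Three other parts of the protocol decide which values exist:
- **Cohort entry (3.4.1).** NCD patients aged six or over "with at least two recorded visits (to enable evaluation of outcomes) will be included in the study cohort". No minimum interval between the visits is given.
- **Testing and attendance (1.1.2).** "Fasting plasma glucose and HbA1c are repeated at 3-monthly intervals for diabetic patients", whereas "Prescriptions are renewed at maximum one-monthly intervals". Section 1.1.6 adds that nurses repeat vital signs at review visits.
- **Home visits (1.1.5).** After an initial monthly phase, "stable patients may be reviewed by phone and visited less frequently".

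The protocol does limit comparable indicators elsewhere. In Table 1 the BP and HbA1c quality indicators refer to the last 12 months. In Table 2 the statin indicator is confined to active patients. The 6- and 12-month BP and HbA1c rows carry neither limit.

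**The concern.** A figure labelled control at 12 months should describe patients at about 12 months. A rule that takes the latest available value returns a result for anyone ever measured, whenever that was. Patients who left early then appear with the control they had when last seen, and nothing in the figure shows that their status at month 12 is unknown.

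HbA1c has a further weakness. A patient can enter the cohort before any repeat HbA1c is due, so the latest value may be the enrolment value. Baseline is then compared with itself.

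The last-visit timing in section 3.4.2 does not resolve this. It pools patients with a month of follow-up and patients with nearly two years, and it is a different quantity from the one in Table 2. The protocol defines effectiveness as quality of care, shown partly through trends in these outcomes, so their definition carries weight.

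**Working it through.** The protocol gives no sample size, power or expected rate for these indicators, so there is no stated figure to reproduce. Three checks follow.

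**1. What a two-visit patient contributes.** Inputs are the monthly maximum prescription interval and the 3-monthly HbA1c (1.1.2), the two-visit rule (3.4.1), and vital signs at review visits (1.1.6). Take a patient seen at months 0 and 1 who does not return.
- HbA1c: the first repeat is due at about month 3. The patient qualifies for the cohort 3 − 1 = 2 months before that. The last HbA1c is the enrolment value, and the trend is exactly 0.
- BP: a post-enrolment reading exists from month 1. It is 6 − 1 = 5 months old at month 6 and 12 − 1 = 11 months old at month 12.

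For BP the exposure is therefore an old value; for HbA1c it can be the baseline itself.

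**2. Who can reach each time point.** Inputs are admissions from January 2015 to the end of December 2016 (3.4.3), patient records over the same period (Executive Summary, study participants), and closure to new patients from May to October 2016 (text after Table 1). Two assumptions are made: records stop at the end of December 2016, and the closure covers both named months.
- Open intake months: 24 − 6 = 18.
- Month 12 within the records: January to December 2015, 12 months. A patient entering on the first day of January 2016 falls on the boundary, so the count is 12, or 13 at the most generous. Not reached: January–April and November–December 2016, 4 + 2 = 6 of 18.
- Month 6 within the records: January 2015 to April 2016, 16 months. Not reached: November–December 2016, 2 of 18.

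These are counts of months, not patients, because monthly intake is not given.

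**3. Illustration of the HbA1c effect.** Let f be the share contributing only the enrolment value, p₀ the proportion at target at baseline and p₁ the proportion at true follow-up. Then

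reported proportion = (1 − f)·p₁ + f·p₀, and the shift = f·(p₀ − p₁).

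None of f, p₀ and p₁ is in the protocol. Assume p₁ = 60% and p₀ = 30% to 50%, and that the patients without a repeat test would otherwise have matched p₁.

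| f | Shift at p₀ = 50% | Shift at p₀ = 30% |
| --- | --- | --- |
| 5% | −0.5 points | −1.5 points |
| 10% | −1 | −3 |
| 20% | −2 | −6 |
| 30% | −3 | −9 |

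For example, with f = 20% and p₀ = 40%: 0.8 × 60 + 0.2 × 40 = 56%, a shift of −4 points.

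**The case against.** The strongest reply is that Table 2 is a list of indicators, and that windows, maximum ages and denominators belong in an analysis plan that is not shown here. A missing window alone would not be a finding. But the protocol does state a rule, most recent or last, and it gives two different timings for the same outcomes. Those two points stand on the protocol alone.

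Several limits on the point are fair:
- A reader might infer that baseline or stale values will be reported as 6- and 12-month results. The text permits this but does not order it. No section says that values are carried forward, and Table 2 mentions baseline separately.
- A reader might infer that BP control could also be scored on the enrolment reading. Repeat vital signs at review visits make that unlikely after two visits.
- A reader might take section 3.4.1 to say that two visits are sufficient for every outcome. It says only that the rule enables evaluation.
- A reader might let every patient without a month-12 HbA1c carry baseline. With 3-monthly tests, someone who leaves at month 7 would carry a month-3 or month-6 value. Only those who leave before the first repeat test carry baseline.
- Home-visit patients are few: 150 against more than 3,500 enrolled, at most about 4.3%. Less frequent visits do not by themselves prove an old BP.

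The protocol also reports patients active at 6 months, the trend in defaulters, and the characteristics of defaulters and deaths. Loss is therefore visible, but not within the control figures.

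**Conclusion.** The point holds as a defect of definition. The Table 2 wording lets values of any age stand as 6- and 12-month control, and it lets the enrolment HbA1c stand as an outcome in diabetic patients who leave before the first repeat test. Section 3.4.2 uses an incompatible timing for the same outcomes.

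The exposure lies with early leavers, defaulters and late entrants. Patients who attend on schedule have recent values and are little affected. If records end in December 2016, late entry alone puts month 12 out of reach for 6 of 18 open intake months and month 6 for 2 of 18.

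The size of the bias is unknown. The shifts of −0.5 to −9 points rest wholly on assumed rates and apply to HbA1c only. For BP even the direction is open, because it depends on how control changed after the last reading. The change is worth making because it is cheap and concerns the principal clinical outcomes.

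**What to change.** - **Align Table 2 and section 3.4.2** on one timing for the principal outcomes. If a last-visit summary is kept, label it as such and give the length of follow-up. The BP threshold is also written differently in the two places (at or below versus below 140/90) and must be reconciled.
- **Use dated windows.** At 6 and 12 months take the post-enrolment value nearest the time point within a stated, non-overlapping window of about ±6 to 7 weeks. A 3-monthly schedule is about 13 weeks. A ±6-week window spans 12 weeks, so it can miss a patient who is off schedule; ±7 weeks spans 14. Around weeks 26 and 52, ±7 weeks gives weeks 19–33 and 45–59, which do not overlap.
- **Limit each time point** to patients enrolled long enough before the data cut-off to reach it, and state the cut-off.
- **Report three categories** at each time point: at target, above target, not measured in window. Defaulters stay in as not measured.
- **For the trend**, require a post-enrolment measurement of that same outcome. Keep the two-visit rule for cohort entry only.

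The cost is wording and a derivation from dated records already held. Fewer patients will contribute a value at each time point. The rate among those measured may still be selective, which is why the not-measured share must be shown beside it. Cholesterol is routinely repeated only once a year, so the 6-month cholesterol indicator is likely to show a large not-measured share.
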